### Data collection methods

The information on history, enrolment, procedures and outcomes is collected using an interviewer-administered pretested structured questionnaire and structured clinical notes. All health workers undertake a standardized 2-day training in misoprostol use for management of incomplete abortion and study procedures. Key areas in the training content include: making a diagnosis of incomplete abortion, use of misoprostol for uterine evacuation, pain relief, post-abortion counseling and values clarification, contraceptive counselling and provision, study procedures, adverse event reporting, danger signs and management of complications. Evaluation of training is done using pre and post knowledge assessments. All research assistants also receive training on research conduct prior to the study. Key areas covered include: research ethical principles, informed consent process, data collection and storage procedures and strategies for retention of study participants. All investigators are trained in good clinical practice. The strategies implemented to promote retention in the study include: clearly informing participants of the study procedure and follow-up schedule, assessing the main outcome before discharge, giving specific follow-up review dates and obtaining at least two phone contacts to ensure communication for follow-up. We conduct continuous process evaluation to ascertain reasons for loss to follow-up, identify and implement context-specific mitigating actions and, in addition, record and analyze reasons for nonadherence or nonretention in the study.

### Sample size

The sample size has been calculated with the objective of establishing the equivalence of misoprostol treatment of incomplete abortion provided by midwives compared with physicians, in terms of the percentage of women not requiring back-up surgical treatment. PASS software version 14 was used for sample size computations for equivalence studies, at a power of 80%, two-sided CI of 95%, set actual difference *D*_1_ range of − 5% to + 5%, smallest difference of 0.001, design effect = 1 and 5% level of significance of results [32]. If a second-trimester abortion treated with misoprostol 400 μg every 6 h administered vaginally has an effectiveness of 90% at 48 h, we assume that the same dose used every 3 h sublingually for second-trimester incomplete abortion would have around 90% effectiveness at 24 h given the faster onset of action for the sublingual route [33]. If both allocation arms have the same success rates within an equivalence margin of 10%, then 566 women will be required in each arm. Considering a loss to follow-up of 5%, 1192 women will be recruited for the study. Table 1 presents the various sample size scenarios, with a δ value of 5% and power of 80% chosen based on the feasibility of accruing the sample size.

**Table 1 Tab1:** Sample size scenarios

δ (%)	Power = 80%	Power = 90%
4	884 (1768)	1183 (2366)
5	566 (1132)	757 (1514)

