### Statistical methods

Statistical analysis will be done using Stata version 13. All analyses will be by intention-to-treat (ITT) supplemented by per-protocol analysis. Background characteristics for the two study groups will be described. Categorical data will be presented as proportions and continuous data as means and standard deviations. To determine the differences in background characteristics, chi-square tests will be used for categorical data and Student *t* tests for continuous data. Analysis of the primary outcome between groups will be done using risk difference with 95% confidence intervals and equivalence established if it lies between the predefined range of − 5% and + 5%. *P* ≤ 0.05 will be considered statistically significant. Chi-square tests will be used for comparison of outcomes and Student’s *t* tests used to compare mean values. Comparisons of side effects will be carried out using Fisher’s exact tests.

We will use a generalized linear mixed-effects model with the provider as a fixed effect and the health care facility as a random effect. This will allow us, to some extent, to take into account differences in performance between the sites. Time to completion of abortion will be computed and analyzed using standard survival analysis techniques. Participants will be censored at the time that the main outcome, a complete abortion, is documented or at 24 h if no complete abortion is achieved. Time in this study will be computed in hours. Median times to completion will be derived from Kaplan–Meier estimates of the survival function and the groups will be compared using the log-rank test. Further analysis will be carried out using a Cox proportional hazards model, which establishes factors associated with time to complete abortion in a multivariable model.

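### The 566 women per arm give about 60% power, not 80%, for the stated equivalence rule, because 566 is the one-bound (non-inferiority) number

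*Protocol article*

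**What the plan says.** The Sample size section ties the calculation to equivalence: "The sample size has been calculated with the objective of establishing the equivalence of misoprostol treatment". Its inputs are given as "at a power of 80%, two-sided CI of 95" (per cent), a range of −5% to +5% that is called the actual difference, a smallest difference of 0.001, and "design effect = 1 and 5% level of significance of results". Success is assumed to be about 90%. The result follows from the clause "If both allocation arms have the same success rates within an equivalence margin of 10" (per cent), "then 566 women will be required in each arm". Allowing 5% for loss to follow-up, this becomes 1192. The text below it says that δ = 5% with 80% power was chosen for feasibility. Table 1 gives 884 and 1183 per arm for δ = 4%, and 566 and 757 for δ = 5%, under columns for 80% and 90% power.

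The decision rule is in Statistical methods, and the Abstract gives it too: "Analysis of the primary outcome between groups will be done using risk difference with 95% confidence intervals and equivalence established if it lies between" −5% and +5%.

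**The concern.** An equivalence claim succeeds only if the lower confidence limit stays above −5 points and the upper limit stays below +5 points. When the true difference is zero, chance can push the interval out on either side, so the probability of failure is the sum of two tails. A sample size that leaves a 20% chance of failure on one side leaves about 40% over both. The figure of 566 looked like a calculation for one side only.

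At stake is the stated chance that the trial meets its primary objective when midwives and physicians truly perform alike. It would miss equivalence about 4 times in 10, where the protocol implies 2 in 10. The choice of δ and power on grounds of feasibility was also made from a table whose power labels do not belong to the equivalence rule.

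**Working it through.** **Inputs.**
- Success of 90% in both arms, true difference zero, limit of 5 points (Sample size).
- Two-sided 95% interval, hence z(0.975) = 1.960 at each limit (Sample size; Statistical methods).
- Allocation 1:1 (Random allocation) and 5% loss (Sample size).
- Variance term 2 × 0.9 × 0.1 = 0.18.

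Unrounded z values are used throughout.

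**Step 1. Reproduce the plan's figure.** The one-bound formula is n = (z(0.975) + z(power))² × 0.18 / δ². At 80% power and δ = 0.05, (1.960 + 0.842)² × 0.18 / 0.0025 = 565.1, so 566 per arm. The loss allowance is 1132 / 0.95 = 1191.6, so 1192. Both match the protocol.

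**Step 2. Check the rest of Table 1.** The last column uses the power formula of Step 4.

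| δ | Column label | One-bound n | Printed | Power for the equivalence rule at printed n |
|---|---|---|---|---|
| 5% | 80% | 566 | 566 | 60% |
| 5% | 90% | 757 | 757 | 80% |
| 4% | 80% | 883 | 884 | 60% |
| 4% | 90% | 1183 | 1183 | 80% |

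All four cells follow the one-bound formula to within one woman.

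**Step 3. Number needed for the stated rule.** With a true difference of zero, the 20% type II error is split over the two sides, so z(0.90) = 1.282 replaces z(0.80): (1.960 + 1.282)² × 0.18 / 0.0025 = 756.5, so 757 per arm. With 5% loss, 1514 / 0.95 = 1593.7, so 1594 recruited.

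**Step 4. Power of the planned size.** Power = 2Φ(0.05/SE − 1.960) − 1, with SE = √(0.18/n).
- n = 566: SE = 0.01783 and 0.05/SE = 2.804, so 2Φ(0.844) − 1 = 60.1%. Exact binomial enumeration with the Wald interval gives 60.5%.
- n = 596: SE = 0.01738 and 0.05/SE = 2.877, so 2Φ(0.917) − 1 = 64.1% (exact 64.2%).
- n = 757: 80.0%.

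As a plain check, the half-width of the interval at 566 per arm is 1.960 × 1.783 = 3.5 points. The observed difference must therefore lie within about ±1.5 points, which is only 0.84 standard errors.

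**Step 5. Could another reading give 566?**
- A 90% interval (5% at each limit) needs 617 per arm, and 566 gives 75%.
- A true difference of 0.001 needs 755 to 762 per arm with the 95% interval, or 615 to 621 with the 90% interval.
- Limits of ±10 points need about 190 per arm.

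None of these returns 566.

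**Step 6. Sensitivity to the success rate.** At 566 per arm and a common rate of 85%, 90%, 92%, 93% and 95%, power is 31%, 60%, 75%, 82% and 94%.

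**The case against.** Several points on the other side carry weight.

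- The primary outcome is assessed at the facility within 24 hours, and assessment before discharge is listed as a retention measure (Data collection methods). Few women may lack it. About 64% may then describe the trial better than 60%. This stands, and both figures should be given, but neither is near 80%.
- Power would reach about 80% if success were near 93% in both arms. This is true, but the protocol assumes 90%, and a lower rate would cost power just as quickly.
- The stated 5% significance level might be read as 5% at each limit. The Abstract, Sample size and Statistical methods all specify a 95% interval, and the looser reading still gives only 75%.
- The error leaves the decision rule, the type I error and the validity of a positive result untouched. This stands in full.

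A reader might infer from the 10% margin that a looser ±10-point threshold is in play. The documents do not support that. Both statements of the decision rule use −5 to +5, the sample size text selects δ = 5%, and 10 is simply the total width of that range. It is loose wording in one sentence.

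A reader might also infer that, because 566 is a non-inferiority number, the trial should be recast as a non-inferiority trial. The Background justifies an equivalence aim, and recruitment began on 14 August 2018 (Trial status). Such a switch would change the hypothesis in a running trial and would not be a correction of wording.

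**Conclusion.** Wrong as written. The 80% belongs to a one-sided 2.5% non-inferiority comparison. For the rule the protocol states, power is about 60% with 566 evaluable women per arm and about 64% with 596, so the claim is too high by roughly 16 to 20 percentage points. The table columns labelled 80% and 90% are about 60% and 80% for equivalence.

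These figures rest on the protocol's own assumptions: 90% success in both arms, zero true difference, 1:1 allocation, design effect 1, and a two-sided 95% interval within ±5 points.

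It would go too far to conclude that the trial is invalid or that a positive equivalence result would be unsafe. What changes is how a negative one is read: failure to show equivalence would be fairly likely even with identical providers, and would not by itself count against care by midwives.

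**What to change.** Keep the recruitment target of 1192 and the rule that the 95% interval must lie within ±5 points. Then correct the Sample size section:

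- State power as about 60% with 566 evaluable per arm and about 64% with 596 per arm, for 90% success in both arms and a true difference of zero. Amend the sentence that says 80% power was chosen.
- Relabel the Table 1 columns as about 60% and about 80%.
- Replace the 10% margin by equivalence limits of −5 to +5 percentage points.
- Describe ±5% as the equivalence limits, not as the actual difference, and give the assumed true difference as 0.

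The cost is wording only, with no extra patients and no change to the analysis, but the stated power becomes less favourable. For comparison, a true 80% under the same assumptions would mean about 1594 recruited, which is 402 more than planned (1594 − 1192).

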### Random allocation

A computer-generated blocked randomization was done by the statistician to generate a randomization list stratified for each study site. The randomization ratio is 1:1 for physicians versus midwives in random blocks of 4–12. The block sizes are not disclosed to the research assistants to ensure concealment. Allocation is concealed using sealed, opaque, sequentially numbered envelopes each containing a serial number and unique study number showing the allocation arm for the individual woman. The randomization list will remain with the statistician throughout the duration of the study and the trial investigators as well as research assistants will not have access to it. Process evaluation is carried out using intermittent check-ups to ensure that the protocol intervention procedures are performed correctly.

### Blinding

Given the nature of the study, the health providers and participants cannot be blinded to the study allocation arm once randomization has occurred. The main outcome assessment is confirmed by an independent assessor who is blinded to the participant’s allocation arm to reduce bias. The data entrants will be blinded to the allocation groups. The Data Safety Monitoring Board (DSMB) will initially be blinded as they conduct the interim analysis, and only unblinded if any safety issues emerge.

### Data management

Data are collected at the study sites in paper case record forms (CRFs) and stored in numerical order in a box file at a secure place. The study coordinator or principal investigator conducts biweekly visits at each of the sites to verify each form for completeness and accuracy. At this point, any missing or inaccurate information is rectified and the checked completed forms brought to the central coordinating center for data entry. Data are double entered into the Epidata version 3.1 study-team-approved soft-copy tool. Provisions (Data Monitoring Plan) have been inserted to check for missing data, with predefined ranges, ensuring use of the correct data format and standardized codes. Any changes (based on discrepancies identified on further cleaning) made to data already entered are only done by authorized personnel and a monthly report indicating the errors cited and corrections made is filed with the project steering committee. Cross-referencing is done with the paper form to ensure completeness of the query correction. A statistician will be involved in analysis of the results.

### Statistical methods

Statistical analysis will be done using Stata version 13. All analyses will be by intention-to-treat (ITT) supplemented by per-protocol analysis. Background characteristics for the two study groups will be described. Categorical data will be presented as proportions and continuous data as means and standard deviations. To determine the differences in background characteristics, chi-square tests will be used for categorical data and Student *t* tests for continuous data. Analysis of the primary outcome between groups will be done using risk difference with 95% confidence intervals and equivalence established if it lies between the predefined range of − 5% and + 5%. *P* ≤ 0.05 will be considered statistically significant. Chi-square tests will be used for comparison of outcomes and Student’s *t* tests used to compare mean values. Comparisons of side effects will be carried out using Fisher’s exact tests.

We will use a generalized linear mixed-effects model with the provider as a fixed effect and the health care facility as a random effect. This will allow us, to some extent, to take into account differences in performance between the sites. Time to completion of abortion will be computed and analyzed using standard survival analysis techniques. Participants will be censored at the time that the main outcome, a complete abortion, is documented or at 24 h if no complete abortion is achieved. Time in this study will be computed in hours. Median times to completion will be derived from Kaplan–Meier estimates of the survival function and the groups will be compared using the log-rank test. Further analysis will be carried out using a Cox proportional hazards model, which establishes factors associated with time to complete abortion in a multivariable model.

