**Methods:**

A randomized controlled equivalence trial implemented at eight hospitals and health centers in Central Uganda will include 1192 eligible women with incomplete abortion of uterine size > 12 weeks up to 18 weeks. Each participant will be randomly assigned to undergo a clinical assessment and treatment by either a midwife (intervention arm) or a physician (control arm). Enrolled participants will receive 400 μg misoprostol administered sublingually every 3 h up to five doses within 24 h at the health facility until a complete abortion is confirmed. Women who do not achieve complete abortion within 24 h will undergo surgical uterine evacuation. Pre discharge, participants will receive contraceptive counseling and information on what to expect in terms of side effects and signs of complications, with follow-up 14 days later to assess secondary outcomes. Analyses will be by intention to treat. Background characteristics and outcomes will be presented using descriptive statistics. Differences between groups will be analyzed using risk difference (95% confidence interval) and equivalence established if this lies between the predefined range of − 5% and + 5%. Chi-square tests will be used for comparison of outcome and *t* tests used to compare mean values. *P* ≤ 0.05 will be considered statistically significant.

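### Randomisation is stratified by site, but the risk difference that decides equivalence has no stated site stratification, and the facility mixed model is not tied to the ±5-point margin

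*Protocol article*

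**What the plan says.** Under Random allocation, the statistician used blocking to "generate a randomization list stratified for each study site", and "The randomization ratio is 1:1 for physicians versus midwives". The Abstract describes the trial as "implemented at eight hospitals and health centers in Central Uganda". Study setting shows that these range from Health Centre IVs to a regional referral hospital.

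Under Statistical methods the primary rule is: "Analysis of the primary outcome between groups will be done using risk difference with 95% confidence intervals", with "equivalence established if it lies between the predefined range of" −5% and +5%. The Abstract attaches the same limits to the risk difference. Neither place says whether the estimate is stratified, weighted or adjusted.

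The next paragraph of Statistical methods adds: "We will use a generalized linear mixed-effects model with the provider as a fixed effect and the health care facility as a random effect". Its stated purpose is: "This will allow us, to some extent, to take into account differences in performance between the sites". The outcome, the link, the effect measure and the model's standing relative to the ±5-point rule are not given.

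Sample size uses two simple proportions at about 90%, a 5-point margin and a design effect of 1.

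**The concern.** A trial that randomises within site is normally analysed within site. Blocking balances the arms inside each facility, so differences between facilities drop out of the true sampling error of the treatment comparison. A risk difference computed from the two pooled arms puts those differences back into its standard error, and its interval is then wider than the design warrants.

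The authors expect site differences, because they add a model for them. That model and the decision rule stand side by side with nothing joining them. If the model used a logit link, it would yield an odds ratio within facilities, which cannot be read against ±5 percentage points without conversion to risks. In an open-label trial it is better that one site-adjusted estimate on the margin's own scale be named as the one that decides.

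At stake are a modest amount of precision and some clarity about which analysis governs if two results fall on either side of a limit.

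**Working it through.** **Inputs from the article.** Success 90% in both arms, margin 5 points, two-sided 95% interval, 566 per arm, 1192 recruited (Sample size); eight sites (Abstract); 1:1 allocation stratified by site (Random allocation). **Assumed:** the spread of success rates between sites, which the article does not give.

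**1. The plan's own sample size.** The usual formula for one bound and two proportions is n = (1.960 + 0.842)² × 2 × 0.90 × 0.10 / 0.05² = 565.1, so 566 per arm. Then 1132/0.95 = 1191.6, so 1192. Both figures reproduce. The formula contains no site term.

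**2. Risk difference without strata.**
- Variance per woman: 0.90 × 0.10 = 0.0900.
- SE = √(2 × 0.0900/566) = 0.01783.
- Half-width = 1.96 × 0.01783 = 0.0350, or 3.50 points.
- Power to place the whole interval inside ±5 points at no true difference: 2Φ(0.05/SE − 1.96) − 1 = 2Φ(0.844) − 1 = 0.601.

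**3. Risk difference stratified by site.** Assume equal-sized sites at 83, 85, 87, 89, 91, 93, 95 and 97%. Their mean is 90% and the variance between them is 0.0021.
- Mean within-site variance: 0.0900 − 0.0021 = 0.0879, which is 2.3% smaller.
- SE = √(2 × 0.0879/566) = 0.01762.
- Half-width = 1.96 × 0.01762 = 0.0345, or 3.45 points.
- Power: 2Φ(0.877) − 1 = 0.620.

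The 60% in step 2 treats the larger SE as the true one. Because allocation is balanced within sites, the crude estimate itself varies with SE of about 0.01762. Its power is then 2Φ((0.05 − 0.03495)/0.01762) − 1 = 0.607. On that stricter comparison the gain is from 61% to 62%.

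**4. Other assumed spreads.** The same method at 566 per arm, with the crude column on the stricter basis. The error column is the actual error per bound of the crude interval, against a nominal 0.025.

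| Between-site SD (points) | Half-width crude → stratified (points) | Power crude → stratified | Error per bound, crude |
|---|---|---|---|
| 0 | 3.50 → 3.50 | 0.601 → 0.601 | 0.0250 |
| 2 | 3.50 → 3.49 | 0.602 → 0.605 | 0.0247 |
| 5 | 3.50 → 3.45 | 0.608 → 0.623 | 0.0234 |
| 7 | 3.50 → 3.40 | 0.614 → 0.644 | 0.0219 |
| 10 | 3.50 → 3.30 | 0.629 → 0.689 | 0.0188 |

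**5. False equivalence.** This was simulated with eight assumed sites of unequal size, 20,000 runs per scenario, at a true difference of −5 points. With between-site SDs of 3.3 and 7.0 points, the crude rule declared equivalence in 2.5% and 2.4% of runs, and the stratified rule in 2.6% and 2.8%. Ignoring the strata does not raise the false-equivalence rate.

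**6. Scale, if the model were logistic.** Odds ratios equal to ±5 points:
- From 90%: (0.85/0.15)/(0.90/0.10) = 0.63 and (0.95/0.05)/(0.90/0.10) = 2.11.
- From 85%: (0.80/0.20)/(0.85/0.15) = 0.71 and (0.90/0.10)/(0.85/0.15) = 1.59.

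The limits move with the baseline risk, so no single pair of odds ratios stands for the margin.

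**The case against.** The strongest reply has three parts.

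First, the article never says that the risk difference is unstratified. A reader might infer a crude analysis from the silence, but the text does not support stating it as fact. It is a condensed article, and the estimator, weights and link could be set out in the full protocol or analysis plan, which are not shown. This part stands, and it limits the point to what the wording leaves open.

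Second, site is not ignored. The mixed model is there for it, and a generalised linear model need not be logistic. With an identity link, or with risks standardised from a logit model, it could itself supply the risk difference. A reader might also infer that an odds ratio is to be compared with ±5 points; nothing in the article proposes that. This part stands too: the scale argument is conditional on a logit link and an unconverted result.

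Third, the harm is small and runs in the safe direction. That is correct, as steps 4 and 5 of the working show. Limitations mentions uneven caseloads but gives no site success rates, so the size of any gain is unknown.

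What the reply does not remove is that the article itself fixes the decision statistic, the margin and the site model, and does not connect them. Naming a stratified estimate is a concrete improvement that follows from how the trial already randomises.

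**Conclusion.** The point holds in a limited form. Randomisation is stratified by site; the ±5-point decision rests on a risk difference with no stated stratification or adjustment; and the facility model has no stated link to that margin.

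If the deciding estimate is computed without strata, the interval is slightly too wide whenever sites differ. With eight equal sites spread evenly over 83–97%, the cost is 0.05 points of half-width and one to two points of power. It is nil if sites are alike, and reaches 0.2 points of half-width and 6 points of power only at a between-site SD of 10 points. All of these spreads are assumptions.

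It would be wrong to conclude that the planned rule risks declaring equivalence too readily; the error is conservative. Two-bound power of about 60% at 566 per arm comes from the one-bound sample-size formula. That is a separate matter and does not make this point more serious.

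Low severity.

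**What to change.** State in the analysis plan, before outcome data are seen by arm, that the deciding estimate is the site-stratified risk difference with its 95% confidence interval, compared with −5 to +5 percentage points. Mantel–Haenszel weights are one suitable choice; standardised risks from a model with site terms are another. Name one of them. Label the crude risk difference and any odds ratio from the mixed model as supportive, with no part in the equivalence decision.

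The cost is a few sentences. Site is known for every woman because she was randomised within it, so no further data, visits or participants are needed.

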### Eligibility criteria

Women with abortion complications presenting with vaginal bleeding, uterine contractions, uterine size more than 12 weeks but no more than 18 weeks by palpation, history of partial expulsion and an open cervical os will be included in the study. We will exclude women with known age younger than 15 years, allergy to misoprostol, unstable hemodynamic status (systolic blood pressure < 90 mmHg) and shock, signs of pelvic infection and/or sepsis, previous caesarean delivery/uterine scar, suspected extra-uterine pregnancy, perforation of the uterus, injury to the surrounding organs, heavy vaginal bleeding, severe abdominal pain, cervical tear, uterine size ≤12 or > 18 weeks, temperature greater than 38 °C and current molar abortion.

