#### Procedure

All assessment and care are provided in a way that ensures privacy and confidentiality. Eligible women who consent undergo a clinical assessment by either a midwife (intervention arm) or a physician (control arm). The clinical assessment includes: history taking (sociodemographic information, last menstrual period (LMP), assessment for chronic medical conditions, obstetric and gynecological history, previous use of contraception and details of presenting symptoms); general physical examination and vital signs (pulse, blood pressure and temperature); and abdominal examination to assess the size of the uterus and a vaginal examination to assess cervical opening, bleeding and signs of genital infections.

The World Health Organization (WHO), in their 2012 safe abortion technical and policy guidance, recommend that the misoprostol regimen for second-trimester termination of pregnancy [6] can be used for incomplete abortion management: 400 μg misoprostol sublingual every 3 h up to five doses. Each treatment dose consists of two 200 μg tablets of misoprostol administered sublingually by the allocated health care provider and this is repeated every 3 h for a maximum of five doses or until a complete abortion is confirmed. The allocated health provider to whom a woman is randomized assesses for presence of side effects, vaginal bleeding and uterine contractions, measures blood pressure and pulse and also records any medication given at 3-h intervals before the next dose of misoprostol is given. The participant completes the full course of treatment under direct observation while at the health facility to ensure adherence. When the participant reports an expulsion, a health provider in the allocated arm performs a clinical assessment to diagnose a complete abortion and records the time of completion, and an independent assessor verifies that the main outcome has been achieved. The expelled products of conception are examined to ascertain the type, whether placental tissue only or whole fetus and placental tissue. All women receive oral nonsteroidal anti-inflammatory drugs starting when the first dose of misoprostol is administered and prophylactic oral antibiotics – amoxicillin 500 mg and metronidazole 400 mg every 8 h for 5 days [30].

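### The primary risk difference is valid but uses no patient-level baseline covariate, so it may forgo a little precision in a decision that turns on interval width

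*Protocol article*

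**What the plan says.** - **Primary analysis** (Statistical methods): "Analysis of the primary outcome between groups will be done using risk difference with 95% confidence intervals", with equivalence declared if the interval lies between −5% and +5%. No baseline covariate is named.
- **Facility** (same section): a "generalized linear mixed-effects model with the provider as a fixed effect and the health care facility as a random effect". The article does not say which outcome this model serves. Its only terms are provider and facility.
- **Other adjustment** (same section): multivariable modelling appears only in the Cox analysis of time to complete abortion.
- **Stratification** (Random allocation): the randomisation list is stratified by study site.
- **Uterine size before allocation:** Eligibility criteria require "uterine size more than 12 weeks but no more than 18 weeks by palpation". Under Enrollment, a trained midwife screens all women against a checklist, and this step comes before consent.
- **Uterine size after allocation:** Procedure lists "abdominal examination to assess the size of the uterus" and an obstetric history as part of the assessment made by the midwife or physician of the allocated arm. Blinding states that providers know the arm.
- **Parity** is not named anywhere.
- **Planning values** (Sample size): a regimen that "would have around 90% effectiveness at 24 h", and "If both allocation arms have the same success rates within an equivalence margin of 10%, then 566 women will be required in each arm".

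**The concern.** In an equivalence trial the whole confidence interval must fit inside the margin, so its width directly affects the chance of a conclusive answer. With a half-width of about 3.5 points, an observed difference beyond about 1.5 points (5 − 3.5) already fails.

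A risk difference standardised over baseline covariates (g-computation from a logistic model) estimates the same marginal quantity on the same scale. In large samples it is no wider than the unadjusted difference, and it is narrower if the covariates predict the outcome. The protocol expects some factors to be associated with time to completion, since it plans a Cox model to find them. The primary outcome, completion within 24 h without surgery, is closely related. Leaving such factors out of the equivalence decision may therefore give up precision that would need no extra women.

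**Working it through.** **Inputs from the Sample size section:** 90% success in both arms, no true difference, margin ±5 points, two-sided 95% interval, 80% power, 566 per arm, 5% loss, 1192 in total. **Assumed, not in the documents:** the share R² of outcome variance explained by the covariates.

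**1. The plan's own figure.** n = 2 × 0.9 × 0.1 × (1.960 + 0.842)² / 0.05² = 566 per arm after rounding up. 566 / 0.95 rounds up to 596 per arm, or 1192 in total. Both stated figures reproduce, using a one-sided formula at 0.025.

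**2. Unadjusted precision.** SE = √(0.18 / 566) = 0.01783. Half-width = 1.96 × 0.01783 = 3.50 points. The chance that both limits lie within ±5 points is 2Φ(0.05 / 0.01783 − 1.96) − 1 = 60.1%.

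**3. Adjusted precision.** The variance is multiplied by (1 − R²), and the same formulas apply at 566 per arm:

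| Assumed R² | Half-width (points) | Chance of showing equivalence | Largest observed difference that passes (points) |
|---|---|---|---|
| 0 | 3.50 | 60.1% | 1.50 |
| 0.01 | 3.48 | 60.9% | 1.52 |
| 0.02 | 3.46 | 61.7% | 1.54 |
| 0.05 | 3.41 | 64.1% | 1.59 |
| 0.10 | 3.32 | 68.0% | 1.68 |

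If all 596 per arm are analysed, the unadjusted chance is 64.1%. It becomes 64.8% at R² = 0.01 and 67.9% at R² = 0.05.

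**4. What such an R² means.** At 90% success, one covariate with an odds ratio per standard deviation of 1.5 gives R² of about 0.015. An odds ratio of 2.0 gives about 0.045, and 3.0 about 0.11. The range 0.01–0.05 thus already supposes a moderately to strongly prognostic covariate.

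**5. In numbers of women.** R² = 0.01 is worth 1132 / 0.99 − 1132 ≈ 11 women in total, and R² = 0.05 is worth 1132 / 0.95 − 1132 ≈ 60.

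**6. Simulation check.** In each scenario 3000 trials were simulated with 566 per arm, comparing logistic g-computation with the plain risk difference. Size was spread evenly over 12–18 weeks and 70% of women were parous (both assumed); site was not modelled. With odds ratios of 0.67 per week and 2.2 for parity (R² about 5%), the chance rose from 60.8% to 65.0%. With covariates of no prognostic value it went from 59.9% to 59.3%, a loss of under one point.

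**7. What adjustment cannot do.** For 80% power under the stated 95% interval rule, n = 0.18 × (1.960 + 1.282)² / 0.05² = 757 per arm. Reaching that power at 566 would need R² ≈ 1 − 566 / 757 ≈ 0.25.

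**The case against.** The case against is substantial.

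- **Nothing is invalid.** An unadjusted risk difference is a proper primary estimate in a randomised trial. Covariate lists are often left to the SAP, which is not shown and may already contain one. This stands, and it limits the point to an efficiency suggestion about the choice that the article states.
- **Prognostic strength is unknown.** A reader might infer that the interval is certainly wider than it need be because uterine size and parity are prognostic. The documents do not say that either predicts complete abortion, and size is restricted to more than 12 up to 18 weeks. This stands.
- **The values may not be usable.** A reader might infer that suitable covariates are already collected for everyone. The uterine size under Procedure is palpated by the unblinded provider of the allocated arm, so it could differ between arms through measurement alone. Parity is only implied by the obstetric history taken at that same assessment. The article does not say that the screening checklist records weeks rather than in or out of range. What survives is that size is an eligibility item, so it has to be judged at screening, before consent.
- **Site.** A model with patient covariates but without the stratification factor would be a poor exchange. Site belongs in it.
- **Type I error.** The simulations used no true difference, so they say nothing about error rates at a true difference of ±5 points, and no such claim is made here.
- **Borrowed importance.** The 60% starting power arises from the sample-size formula, not from the lack of covariates. This stands too.

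**Conclusion.** The point holds as a modest efficiency improvement. The stated primary analysis is valid but has no patient-level covariate. A standardised risk difference would keep the scale, the estimand and the margin, and would probably be slightly narrower. At an assumed R² of 0.01–0.05 the half-width falls by 0.02–0.09 points and the chance of showing equivalence rises by about 1–4 percentage points. If the covariates are not prognostic, almost nothing is gained or lost.

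These figures rest on 90% success, no true difference, 566 analysed per arm, and an R² that the documents do not supply. A reader might infer that adjustment would restore the stated 80% power. It would not, since that needs an R² of about 0.25; the power shortfall is a separate matter.

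**What to change.** Before unblinding, prespecify as the primary estimate the marginal risk difference standardised from a logistic model with arm, study site and uterine size in weeks. Specifically:

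- Take uterine size from the pre-allocation eligibility screening, provided the checklist records weeks. The sponsor should confirm this.
- Do not use the size palpated by the allocated provider at the clinical assessment described under Procedure.
- Add parity only if it is recorded, and recorded independently of the allocated provider.
- Use a robust 95% confidence interval, judged against the same ±5 points.
- Report the unadjusted risk difference as a sensitivity analysis.

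The cost is a few lines of SAP wording and Stata code, slightly more complex reporting, and covariates that must be fixed in advance. At 90% success about 113 failures are expected (0.10 × 1132) over eight sites with uneven caseloads, so a rule for sites with very few failures should be written down too. Recruitment began in August 2018, so if the checklist does not record weeks, programming cannot recover the value for women already enrolled. Adjustment would then be for site alone.
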